#### Overall survival (OS)

The period beginning on the date of the first postoperative administration of S-1 and ending on the date of death from any cause.

In surviving cases, the last date of confirmation of survival is the date of termination (telephone confirmation of survival is also acceptable, but should be documented in the patient's medical record). (Survival confirmation by phone call is also acceptable, but the fact that the patient survived must be recorded in the patient's medical record.)

In the case of untraceable cases, the last date of confirmed survival prior to the loss of follow-up is considered to be the termination date.

Differences in survival stratified by percentage of completion will also be identified.

#### Percentage of occurring adverse events (adverse reactions)

Using all treated cases as the denominator and the incidence of adverse events judged to be caused by the study treatment as the numerator, the proportion of the worst grade in the entire course according to the CTCAE v4.0 of the Japanese translation JCOG version is determined.

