### 0.2. Purpose

To evaluate the tolerability and efficacy of alternate-day administration of S-1 as postoperative chemotherapy in elderly patients with completely resected pathological stage IA (T1bN0M0)/IB/II/IIIA non-small cell lung cancer.

Primary endpoint: Completion rate (Feasibility)

Secondary endpoints: rate and severity of adverse events, recurrence-free survival (RFS), overall survival (OS), quality of life (QOL)

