## 1. Purpose

To evaluate the tolerability and efficacy of alternate-day administration of S-1 as postoperative chemotherapy in elderly patients with completely resected pathological stage IA (T1bN0M0)/IB/II/IIIa non-small cell lung cancer.

Primary endpoint: Completion rate (Feasibility)

Secondary endpoints: rate and severity of adverse events, recurrence-free survival (RFS), overall survival (OS), quality of life (QOL)

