### **9.2. Definition of adverse events**

An adverse event is any unwanted or unintended sign (including abnormal changes in laboratory values), symptom, or illness that occurs in a subject as a result of receiving the study treatment, whether or not causally related to the study treatment.

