### **9.3. Assessment of adverse events/adverse reactions**

The NCI Common Terminology Criteria for Adverse Events v4.0 (Japanese translation; attached) will be followed. An adverse event is defined as a Grade 1 or greater deterioration from the baseline level.

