### **9.5. Causal relationship with study drug**

In determining the causal relationship of an adverse event to the study drug, the subject's general condition, complications, concomitant medications/adjunctive therapies, and temporal relationship should be taken into consideration. The causal relationship will be judged by using two categories: "there is a reasonable causal relationship with the study drug" and "there is no reasonable causal relationship with the study drug". Among adverse events, those with a reasonable causal relationship to the study treatment shall be treated as adverse reactions.

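### The adverse-event endpoint is computed only from events attributed to S-1, contrary to its name and to Section 9, so differential attribution could distort the toxicity comparison between arms

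*Protocol*

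**What the plan says.** Sections 0.2, 1 and 12.1 list "rate and severity of adverse events" as a secondary endpoint.

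The computing rule is in Section 12.2, under the heading on the percentage of adverse events, which carries adverse reactions in parentheses. The rule reads "Using all treated cases as the denominator" and takes "the incidence of adverse events judged to be caused by the study treatment as the numerator". The proportion at each worst CTCAE v4.0 grade over the whole course is then determined.

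Section 9 sets the vocabulary:

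- **9.2** covers events "whether or not causally related to the study treatment", although the same sentence also describes them as resulting from the study treatment.
- **9.3** has no causality condition: "An adverse event is defined as a Grade 1 or greater deterioration from the baseline level".
- **9.5** adds the attribution step. "The causal relationship will be judged by using two categories", and "those with a reasonable causal relationship to the study treatment shall be treated as adverse reactions". It does not say who judges.

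In Section 13.4, rule (3) applies when one arm's completion rate exceeds 40% and the arms differ by no more than 15%. Toxicity is then one of seven considerations for choosing the schedule to take into Phase III. The others are quality of life, convenience, cost, retention after 6 months, recurrence-free survival and survival.

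**The concern.** The objectives promise one quantity and the evaluation section computes another. In the protocol's own terms the objectives name adverse events, while the computed measure is adverse reactions. The protocol makes no all-cause tabulation the endpoint, so an analyst who follows Section 12.2 produces only the attribution-filtered figures.

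The filter is a yes/no judgement, and Section 9.5 asks that general condition, complications and concomitant medication be weighed in making it. Arm A takes S-1 on four fixed weekdays and Arm B takes it daily for 14 days followed by 7 days' rest, so whoever judges can tell the arms apart unless shielded. The protocol describes no such shielding. Section 13.4 also states a directional aim, to verify that the alternate-day schedule is superior in continuity. Patients are at least 75 years old and have had a lobectomy or more, so some symptoms have plausible causes other than the drug.

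Two things are at stake. Absolute toxicity in an elderly population may be understated. A gap in attribution between the arms could also appear as a toxicity difference in the comparison used to choose a schedule.

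**Working it through.** **Step 1. Set the sections side by side.**

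| Section | What it fixes | Causality condition |
|---|---|---|
| 0.2, 1, 12.1 | Endpoint name: adverse events | None |
| 9.2 | Definition of adverse event | Internally inconsistent: resulting from treatment, yet regardless of causality |
| 9.3 | Any Grade 1 or greater worsening from baseline | None |
| 9.5 | Attributed events are termed adverse reactions | Yes |
| 12.2 | Numerator of the endpoint | Yes |

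Section 12.2 agrees with the 9.5 term and disagrees with the endpoint name and with 9.3. The clearest contradiction is with 9.3, because 9.2 is not clean enough to serve as the benchmark alone.

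**Step 2. What an attribution filter does to a comparison.** The protocol gives no toxicity rate and no attribution rate for this trial, so there is no stated figure to reproduce and every rate below is an assumption. Let p be the all-cause rate of Grade 3 or higher events, equal in both arms, and let a_A and a_B be the proportions attributed to treatment.

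- Expected reported rates are p × a_A and p × a_B.
- The false difference is p × (a_B − a_A), and the true difference is 0.
- With p = 0.30, a_A = 0.60 and a_B = 0.80: 0.30 × 0.60 = 18% and 0.30 × 0.80 = 24%, a false difference of 6 points.
- With p = 0.30 and gaps of 10 to 30 points: 0.30 × 0.10 = 3 points, up to 0.30 × 0.30 = 9 points.

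The next table varies p and the gap. It takes 50 patients per arm (the planned 100 split equally, also an assumption). The last column is the exact binomial probability that Arm A shows the lower reported rate, with ties split evenly.

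| p | a_A | a_B | False difference | P(Arm A looks less toxic) |
|---|---|---|---|---|
| 20%, 30% or 40% | 80% | 80% | 0 points | 0.50 |
| 20% | 70% | 90% | 4 points | 0.71 |
| 30% | 70% | 90% | 6 points | 0.76 |
| 40% | 70% | 90% | 8 points | 0.80 |
| 20% | 50% | 90% | 8 points | 0.88 |
| 30% | 50% | 90% | 12 points | 0.93 |
| 40% | 50% | 90% | 16 points | 0.96 |

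Swapping a_A and a_B reverses the sign. Equal attribution gives no false difference, but both arms then under-report: 24% instead of 30% at p = 0.30 and 80% attribution.

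**Step 3. How often rule (3) would apply.** Inputs are the completion rates in Section 13.3, 55% and 40%. The exact binomial probability that at least one observed rate exceeds 40% and the two differ by no more than 15 percentage points is:

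- 55% v 40%: 0.48 with either 37 or 50 per arm.
- 55% in both arms: 0.80 with 37 per arm, 0.87 with 50 per arm.

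So toxicity enters the schedule choice in about half of trials under the design assumption, and in most trials if the arms do not differ.

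**The case against.** The best defence is that Section 12.2 discloses the restriction. Its heading carries the term adverse reactions, Section 9.5 defines that term, and tabulating treatment-related toxicity is a recognised choice. On this view the fault is a naming mismatch in a translated document, and a supplementary all-cause table could sit in the analysis plan. Part of this stands: a treatment-related table is legitimate. But the protocol itself fixes the numerator, and fixes it against the endpoint name, so this is not a detail left open.

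Several stronger readings are tempting, and the protocol does not support them:

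- **That the treating physician decides causality.** Section 9.5 names no judge. Section 10.3 says only that the physician in charge completes the urgent report. Section 10.4 sends reportable events to the Data and Safety Monitoring Committee. What can be said is that no blinded or independent attribution is described for routine events.
- **That the bias favours the alternate-day arm.** Both arms take the same drug from the same starting-dose table, and nothing shows that attribution differs by schedule. It could run either way or be absent.
- **That toxicity leads rule (3).** It is named first, but the list is unranked and unweighted and sets no toxicity threshold.
- **That Section 9.2 is a clean all-cause definition.** Its sentence contradicts itself.

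There are also partial safeguards. Section 9.3 counts only worsening from baseline, and Section 11.3 records symptoms before treatment, which removes stable post-surgical complaints. Many of the graded toxicities are laboratory values, where judging whether an event occurred leaves less room. Section 10.1 requires all deaths up to 30 days after the last treatment to be reported whatever their cause. These narrow the exposure but do not remove the attribution filter from the endpoint.

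**Conclusion.** The point holds as an inconsistency in how a secondary endpoint is defined, with a possible consequence for the choice of schedule. Section 12.2 computes adverse reactions where Sections 0.2, 1 and 12.1 promise adverse events, and it contradicts Section 9.3 and the causality-free clause of 9.2. That much rests on the text alone.

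The consequence rests on an inference: visibly different schedules, with no blinding or independent attribution described, leave room for attribution to differ by arm. The direction and size are unknown. The 3 to 9 points, and the wider range in the table, are products of assumed rates and show only what the rule permits.

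The primary endpoint is unaffected, and the defect can be repaired at analysis. It should still be corrected, because the toxicity comparison can bear on which schedule goes to Phase III.

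**What to change.** 1. In Section 12.2, define the endpoint as the worst CTCAE grade per patient of all adverse events regardless of attribution, in all treated cases, by arm.
2. Use the treatment period already defined in Section 11.1 as the window, and reconcile it with the adverse-event follow-up in Section 7.2. The former runs from enrolment to 4 weeks after the last dose, or to the start of post-treatment if earlier. The latter can run until events resolve or stabilise.
3. State in Section 13.4 that the toxicity comparison in rule (3) uses this all-cause table.
4. Report treatment-related events as a second table, and state in Section 9.5 who judges causality.
5. Reconcile Sections 9.2 and 12.2, including the self-contradiction inside 9.2.

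The cost is about one extra table, and reported rates will be higher. Section 13.2 already makes all treated cases the safety population. Section 15.1 collects blood tests and abnormal subjective and objective findings with no stated causality filter, so the change should need no new data collection.

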### **13. Target cases and study period**

#### **13.1. Case accumulation period/follow-up period**

Case collection period: May 2012 – April 2016 (4 years)

Follow-up period for primary endpoint: 6 months after the end of enrollment

Research period: April 2012 – June 2022

All endpoints will be analyzed 6 months after the end of enrollment, when the protocol treatment and completion rates of all enrolled patients have been assessed. Survival analyses for secondary endpoints will be conducted at 2 years and at the end of the 5-year follow-up period after the end of enrollment. The data center will be responsible for conducting the analyses until the second year after the completion of the final case enrollment, and the secretariat will conduct the analyses thereafter, to be finalized upon consultation with the secretariat. After the analysis of the primary endpoint of the study is completed, the data center will, upon request of the secretariat, transfer to the secretariat free of charge all data information and analysis results related to the study that exist at the data center, as long as it is judged that there will be no bias in the publication of the results or in the analysis of secondary endpoints. The data center shall transfer all data information and analysis results related to the study that exist at the data center to the secretariat free of charge upon request of the secretariat.

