## 6. Protocol treatment

### 6.1. Overview

The alternate-day administration of S-1 and 2-week administration of S-1 followed by 1-week rest are defined as protocol treatment in this study. As a rule, protocol treatment will be initiated within 1 week after enrollment and within 8 weeks after surgery. If more than 8 weeks have elapsed since surgery, the data center will be contacted to confirm whether protocol treatment can be started, and if so, it will be initiated. After initiation, the reason why the treatment could not be started within 8 weeks should be noted in the comment section of the “Report of Study Initiation and Pre-Treatment Discontinuation”. TS-1 should be TS-1 combination capsules T20, T25, TS-1 combination granules T20, T25, and TS-1 combination OD tablets T20, T25 (Taiho Pharmaceutical Co).

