### 6.2.7. Criteria for completion of protocol treatment (Arm A)

Protocol treatment is terminated when one year has elapsed from the date of the first administration of S-1 as adjuvant chemotherapy after surgery for lung cancer.

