### 6.3. Arm B: S-1 2-week administration followed by 1-week rest method

#### 6.3.1. Treatment schedule for Arm B (S-1 2-week administration followed by 1-week rest method)

**Administration cycle:** Oral administration every day for 14 consecutive days from Day 1 (after dinner on Day 1 to after breakfast on Day 15)

The drug is then withdrawn for 7 days, and this is repeated every 3 weeks for one course.

**End date of treatment:** Administration should be performed until the total treatment period from the protocol treatment start date has reached 12 months. No new courses should be started after the same calendar day 12 months after the protocol treatment start date. The final course of treatment should be administered until a date equivalent to day 14.

[figure not shown]

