## **15. Data collection and storage**

### **15.1. Data collection**

The Case Report Forms (CRFs) to be used in this study and the submission deadlines are as follows. In principle, all CRFs below should be sent by mail. All CRFs should be sent to the data center.

- (1) Basic subject data: Promptly after registration
- (2) Anticancer Drug Administration Record Form: At the time of discontinuation of treatment/within 2 weeks after completion
- (3) Treatment Termination Report Form: At the time of discontinuation of treatment/within 2 weeks after completion
- (4) Follow-up: Every 1 year or upon confirmation of recurrence
- (5) Blood tests, abnormal subjective and objective findings, abnormal values, etc.: At the time of discontinuation of treatment/within 2 weeks after completion
- (6) Tracking Report Form: At the time of request of the secretariat

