### **21.2. Method of investigation**

Patients complete a prescribed QOL questionnaire over a 12-month period from enrollment.

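### Section 13.1 schedules all non-survival endpoints for 6 months after enrolment ends, before 12-month treatment can be assessed in late enrollees, and 15.1 schedules no six-month dosing form for the primary endpoint

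*Protocol*

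**What the plan says.** **Timing.** Protocol 13.1 gives "Follow-up period for primary endpoint: 6 months after the end of enrollment". It later states that "All endpoints will be analyzed 6 months after the end of enrollment", and adds that by that date treatment and completion will have been evaluated for everyone enrolled. The next sentence gives survival its own dates, 2 and 5 years after enrolment ends. No other endpoint is exempted.

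**Treatment length.** Arm A (6.2.7): "Protocol treatment is terminated when one year has elapsed from the date of the first administration of S-1". Arm B (6.3.1): "Administration should be performed until the total treatment period from the protocol treatment start date has reached 12 months", with the last course run to its day 14. Section 7.3 also describes completion of protocol treatment as one year in both arms. On the start of treatment, 6.1 says that as a rule "protocol treatment will be initiated within 1 week after enrollment and within 8 weeks after surgery".

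**Endpoints.** The primary endpoint (12.2) is six months of S-1 with at least 70% of the planned dose taken. Section 12.2 also asks for completion at 9 months and 1 year, and for the worst toxicity grade over the whole course. For QOL (21.2): "Patients complete a prescribed QOL questionnaire over a 12-month period from enrollment".

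**Forms.** Section 15.1 lists "Anticancer Drug Administration Record Form: At the time of discontinuation of treatment/within 2 weeks after completion". The treatment termination report and the form for blood tests and abnormal findings have the same due date. Nothing is scheduled at six months. A tracking form may be requested by the secretariat, but its content is not stated.

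**The concern.** The analysis date in 13.1 fits a six-month treatment, but the treatment lasts twelve. Two consequences follow.

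First, several endpoints that 13.1 places at that date need up to 12 months of observation per patient. No change in data handling can supply them for patients enrolled late.

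Second, the primary endpoint is observable by then in nearly everyone, but the record needed to compute it is tied to the end of treatment. A late enrollee who stops early has a dosing form due. One who passes month 6 and stays on S-1 may have none due for another six months. Whether a form is due then depends on the outcome itself, in an endpoint that 13.4 compares with a fixed 40%.

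**Working it through.** **Plan's own figure.** Section 13.3 gives 37 per group for a 90% probability of correct selection at 55% versus 40%. The exact binomial P(better > worse) + ½P(tie) is 89.9% at n = 36 and 90.2% at n = 37. The figure reproduces, so 55% and 40% are used below.

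**Endpoints against the 6-month cut-off, for the last enrollee**

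| Endpoint | Observation needed | Available? |
|---|---|---|
| Six-month completion | 6 months from first dose | Short by the start lag, up to about 1 week |
| 9-month and 1-year completion | 9 and 12 months | No |
| Worst grade, whole course | 12 months of treatment (11.1 extends the treatment period to 4 weeks after the last dose) | No |
| QOL | 12 months from enrolment | No |

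The start lag affects about 1 week / 208 weeks × 100 = 0.5 of 100 patients under four-year accrual.

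**Who has no form due, if completion in 15.1 means one year.** The form falls due 12 months after first dose, plus 0 to 3 weeks (start lag up to 1 week, form window up to 2 weeks). Patients still on S-1 who enrolled in the last 6.0 to 6.7 months therefore have none due. With even accrual (assumption) over the 48 months in 13.1:

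- 6.0/48 = 12.5% and 6.69/48 = 13.9%, so 12.5 to 13.9 of 100 patients. This is an upper limit, because early stoppers among them do have forms due.
- Completers without a form, per 50 patients: 50 × 0.55 × 0.125 to 0.139 = 3.4 to 3.8 in a 55% arm; 50 × 0.40 × 0.125 to 0.139 = 2.5 to 2.8 in a 40% arm.

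**Effect if only forms due by the cut-off were used (assumption).** With p the true completion rate and g the share of completers with no form due, the observed rate is p(1−g) / [p(1−g) + (1−p)].

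- p = 0.55, g = 0.125: 0.481/0.931 = 51.7%; g = 0.139: 51.3%.
- p = 0.40, g = 0.125: 0.350/0.950 = 36.8%; g = 0.139: 36.5%.
- Difference: 51.7 − 36.8 = 14.9 points (14.8 from unrounded rates), and 51.3 − 36.5 = 14.8 points, against 15 planned.

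**Sensitivity**

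- If only 80% of those completers are still on treatment (assumption): about 52% and 37%.
- If a missing form were counted as non-completion: 0.55 × 0.875 = 48.1% and 0.40 × 0.875 = 35.0%, a gap of 13.1 points.
- Section 13.3 still gives a 2-year enrolment. On that figure 25 to 27.9 of 100 patients are affected, and the forms-only rates are about 47–48% and 33%.

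**Against the 40% threshold.** For a true 55% arm with n = 50, the chance of observing 19 or fewer completers (below 40%) is 1.2%. At an expected rate of 51.4% it is about 4%. Keeping n = 50 is an approximation, since the denominator would also shrink.

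**The case against.** **Only the date of the analysis is fixed, not the handling of missing forms.** The protocol nowhere says that patients without a form are dropped or counted as failures. The clause about all patients having been assessed can be read as a condition for starting the analysis. Section 20 allows the primary report up to a year after primary data collection ends, about 18 months after enrolment, while the last completer's form is due at about 12.7 months. This stands: a downward bias is conditional, not established.

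**Completion in 15.1 may mean the six-month definition.** Section 12.2 defines completed administration at six months, and 7.3 refers to 12.2 for detail, although 7.3 itself says one year. On the six-month reading only a window of about 3 weeks is late, 3/208 × 100 = 1.4 patients. This stands as a possible reading; even then the last forms fall due after the cut-off.

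**The decision rules.** A reader might infer that rule (3) of 13.4 would be applied to half-observed toxicity, QOL and later retention. The text does not support that. The rules are applied when the trial ends, and rule (3) also uses survival outcomes that are dated years later.

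**Loose wording.** It may be said that the reference to all endpoints is only shorthand, since survival is dated separately and 13.2 mentions safety in the final analysis. But no other date is given for QOL, whole-course toxicity or 9- and 12-month completion.

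**Conclusion.** The timing statement in 13.1 is wrong as written. Six months after enrolment ends, protocol treatment cannot have been assessed in late enrollees who are still on it, and three sets of endpoints placed at that date cannot be complete. This needs no assumption beyond the protocol's own durations.

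For the primary endpoint the defect is narrower. Follow-up is adequate to within about a week, but no dosing form is scheduled at month 6. Under the one-year reading of completion and even four-year accrual, at most about 12 to 14 of 100 patients could reach the cut-off on treatment with no form due. If the analysis then relied only on forms due, 55% would appear as about 51–52% and 40% as about 37%.

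A reader might infer that the arm comparison is distorted or that a good arm would probably fail. Neither follows. On forms due, the difference stays near 15 points, and a true 55% arm would fall below 40% about 4% of the time instead of 1.2%. What is exposed is the absolute 40% threshold, chiefly for an arm whose true rate lies close to it.

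**What to change.** - **15.1:** require the Drug Administration Record and the blood test/adverse event form at six months from first dose for every patient, as well as at the end of treatment.
- **0.5 and 13.1:** set the primary cut-off at six months after the last patient's first S-1 dose, plus the two-week form window.
- **13.1:** replace the reference to all endpoints with the primary endpoint. Analyse adverse events, QOL and 9- and 12-month completion no earlier than about 13 months after the last first dose (12 months of treatment plus 4 weeks), allowing up to about two weeks more if a final Arm B course runs past month 12.

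Cost: one extra form submission per patient, about three weeks' delay to the primary analysis (start lag of 1 week plus form window of 2 weeks), and about 13 − 6 = 7 months' delay to the non-survival secondary endpoints. With enrolment ending in April 2016 and the research period running to June 2022, this fits easily.
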